### Sample size and statistical analysis

The primary outcome measure will be VAS under activity measured on a continuous 100 mm scale 12 month after the operation. Clinically important differences between the two groups is detected to be 18 mm [46, 47]. Based on earlier studies we assume a common standard deviation between participants of 19 mm on VAS [2, 10, 48]. With a significance level at 0.05 and the power at 0.90 the study needs 23 patients in each arm. Taking into account a loss to follow-up after 1 year on approximately 20% we aim at including 28 patients in each group a total of 56 patients.

Clinical and demographic characteristics as well as baseline data will be presented to show the baseline comparability of the two groups. Data from the patients who withdraw from the study will also be examined. For each group descriptive statistics will be presented at baseline and three and 12 months postoperative. Normally distributed data are described by means and standard deviation (SD), and data not normally distributed by medians and interquartile range (IQR). The primary analysis will use the intention-to treat principle including all randomised participants. Patients who discontinue the intervention will be encouraged to participate in the follow up test anyway, and those who accept will be included in the analyses according to their original group assignment. The primary outcome pain is measured on a continuous scale and between-group mean differences and 95% confidence intervals from baseline to 3 and 12 months will be analyzed by a mixed effects linear regression model with a random person level and systematic effects of time, group and the interaction between time and group. We will employ multiple imputation methods in order to assess the sensitivity of the mixed model to any informative missing values. Imputations will be performed using baseline characteristics and non-missing pain measurements on individual levels. Secondary outcomes will be analysed as above for normally distributed measures or for binary outcomes, we will use logistic regression with a robust variance estimate to account for the repeated measurements. Standard diagnostic plots will check model assumptions. The statistical analyses will be performed using STATA 13 (StataCorp, College Station, TX) software package. The significance level will be set at 0.05.

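### The listed imputation predictors do not name randomised group; run as written, the missing-data sensitivity analysis would understate any true 12-month difference

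*Protocol article*

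**What the plan says.** All relevant text is in the protocol article, section Sample size and statistical analysis.

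- The primary analysis of VAS pain is a "mixed effects linear regression model with a random person level and systematic effects of time, group and the interaction between time and group".
- The purpose of the imputation is given as: "We will employ multiple imputation methods in order to assess the sensitivity of the mixed model to any informative missing values".
- The predictors are given as: "Imputations will be performed using baseline characteristics and non-missing pain measurements on individual levels".

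Randomised group is not among the named predictors, and imputation by arm is not mentioned. No other section adds detail on the imputation. The same section expects about 20% loss to follow-up at one year, and pain is collected at baseline, 3 months and 12 months (Outcome assessment, Table 2).

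**The concern.** An imputation model should contain the effect that the analysis model estimates. Here the analysis model has "systematic effects of time, group and the interaction between time and group", while the imputation list has only pre-operative information and the patient's own observed pain scores. Without arm, a missing 12-month score in either arm is drawn from one pooled regression. The imputed values then carry only as much of the arm difference as shows through an observed 3-month score, and none of it when that score is also missing.

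This is the only missing-data sensitivity analysis the article describes for the primary outcome, in a trial of 56 patients. If it gives a smaller difference than the mixed model, the reader should be able to attribute the gap to the missing data. Run as listed, it would give a smaller difference even with data missing completely at random, so an artefact of the imputation model could not be told from a real missing-data problem.

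**Working it through.** **Inputs from the article.** Difference 18 mm ("Clinically important differences between the two groups is detected to be 18 mm"); SD 19 mm ("we assume a common standard deviation between participants of 19 mm on VAS"); about 20% loss at one year; 28 patients per arm.

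**Assumptions not in the article.** Equal correlation between visits, 0.3 to 0.7; a 3-month effect of 0, 9 or 18 mm; 0 to 20% missing at 3 months, all of these patients also missing at 12 months; data missing completely at random and equally in both arms.

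**Step 1. The plan's own figure.** Two-sided alpha 0.05 (sidedness is not stated) and power 0.90: n = 2 × [19 × (1.960 + 1.282) / 18]² = 23.4 per arm, against the stated 23. Then 23 × 1.20 = 27.6, so 28 per arm. The figure reproduces to within rounding, and the point below does not depend on it.

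**Step 2. Lower end of the range.** If the observed pain scores carry no arm information (no 3-month effect, or no 3-month score for the dropouts), the imputed values have the same mean in both arms:

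estimate = (1 − 0.20) × 18 + 0.20 × 0 = 14.4 mm, an attenuation of 3.6 mm or 20%.

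**Step 3. When every dropout has a 3-month score.** Let b be the slope on the 3-month score in the pooled regression of the 12-month score on baseline and 3-month VAS, and let d be the 3-month effect:

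estimate = 0.80 × 18 + 0.20 × b × d

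Pooling the arms adds d²/4 to the 3-month variance and d × 18/4 to the covariance of the 3- and 12-month scores. With V = 19² = 361 and c = correlation × 361:

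b = [(c + d × 18/4) × V − c²] / [V × (V + d²/4) − c²]

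For correlation 0.5 and d = 18: c = 180.5, and b = (261.5 × 361 − 180.5²) / (361 × 442 − 180.5²) = 61,821 / 126,982 = 0.487. The imputed difference is 0.487 × 18 = 8.8 mm, and the estimate is 14.4 + 0.20 × 8.8 = 16.2 mm.

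**Step 4. Check by simulation.** Regression-based multiple imputation with proper parameter draws, 4,000 patients per arm, no 3-month scores missing:

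| Correlation | 3-month effect (mm) | Formula, no arm (mm) | Simulated, no arm (mm) | Simulated, arm included (mm) |
|---|---|---|---|---|
| 0.3 | 0 | 14.4 | 14.5 | 18.1 |
| 0.3 | 18 | 15.8 | 15.7 | 17.9 |
| 0.5 | 9 | 15.2 | 15.3 | 18.0 |
| 0.5 | 18 | 16.2 | 16.2 | 18.0 |
| 0.7 | 18 | 16.5 | 16.6 | 18.1 |

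When all 20% also lacked a 3-month score, the simulated estimates without arm were 14.2 to 14.6 mm, which is the 14.4 mm of Step 2 within simulation error. Over all settings, the estimates with arm included were 17.8 to 18.2 mm.

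**Step 5. Planned size.** With 28 per arm, four settings gave means of 14.2 to 16.3 mm without arm and 17.7 to 18.1 mm with arm.

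**Step 6. No true difference.** With a true difference of zero, the mean estimate was 0.04 mm without arm and 0.02 mm with arm, so there is no bias.

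**The case against.** The strongest reply is that the sentence does not exclude arm. It is one line in a condensed article. It does not say that the list is complete or that the arms are pooled, and an analyst may well include arm or impute by arm, as a full analysis plan might specify. This stands in part: a reader might infer that the plan excludes randomised group, and the text does not go that far. But the article does not leave the model open either. It names predictors, it names group in the model being checked, and it does not treat group as a baseline characteristic: "baseline data will be presented to show the baseline comparability of the two groups" makes baseline data the thing compared across groups. If arm was always intended, the published sentence still misdescribes the method.

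Two further inferences go too far.

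- A reader might think the trial's main result is biased. It is not: the primary mixed model contains group, and the imputation is only a check on it.
- A reader might conclude that a true effect would be declared fragile. This has not been shown. The article sets no rule for such a judgement, and no probability of a changed conclusion was calculated. On a rough standard error of 19 × √(2/22) = 5.7 mm for 22 completers per arm, even an average estimate of 14.2 mm exceeds 1.96 × 5.7 = 11.2 mm.

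It is also fair that the size rests on assumed correlations and 3-month data, and that the bias is toward no difference, so it cannot create an effect.

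**Conclusion.** The concern holds conditionally and is confined to the sensitivity analysis. If the imputation uses only the named predictors and a true difference exists, the 12-month estimate is attenuated. At 18 mm and about 20% loss it falls to about 14.4 to 16.6 mm, a shift of 1.4 to 3.6 mm (8% to 20%). The missing fraction caps the attenuation, and it is smallest when dropouts have 3-month scores that already show the effect. The direction and the 14.4 mm end follow from the article's own figures; the position within the range depends on the assumptions listed in the check. It is worth correcting because a robustness check that moves for a technical reason cannot do its job, and the correction is nearly free.

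**What to change.** Amend the imputation sentence to state that randomised arm is in the imputation model and that VAS at each visit is imputed in a model that lets the arm effect differ by visit. Imputing each visit's score from its own regression, with arm as a predictor, achieves this. Imputing separately by arm is an acceptable alternative, at a small loss of precision because each model then rests on about 22 observed patients (28 × 0.80 = 22.4).

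The cost is one sentence and a small change to the imputation command. Sample size, data collection and the primary analysis do not change. The choice of baseline predictors can stay as it is.

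One limit: imputing from observed data assumes missingness at random with or without arm. This change removes the artefact, but does not by itself make the analysis a test of informative missingness.

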### Ethical considerations

The study is approved by The Central Denmark Region Committee on Biomedical Research Ethics (journal no. 1-10-72-64-15) and The Danish Data Protection Agency and is registered at www.clinicalTrials.gov (NCT02587429). The study will be conducted in accordance with the Good Clinical Practice Guidelines and the Declaration of Helsinki. All patients are ensured minimum standard treatment and the patient education carries no risk to the patients.

## Discussion

Knee OA is one of the most common forms of arthritis and an increasing proportion of older people have to live with chronic diseases in the future. This will carry a major economic burden for the healthcare system and recent research shows that there is high need of developing treatments aimed at improving self-management for a selected group of patients at high risk of having long-term pain and physical disability after a TKA. CBT interventions are traditionally delivered by psychologists and using physiotherapists to deliver psychological interventions is fairly novel. However, physiotherapists have a history of teaching patients about pain and pain coping. Further, they normally see the patients several times in connection with the operation and taken into account the high number of TKA operations and the limited availability of psychologists at the hospital physiotherapists are highly qualified to provide this patient education. Recent studies shows that both nurses and physiotherapists are sufficient to deliver high standard pain coping skills training [17, 49].

This study design has several strengths. First, the patients are screened on basis of their risk of having chronic pain after the operation. Only patients with high levels of pain catastrophizing will be eligible for the patient education and the education will be targeted these patients. Second, the outcome measures are valid and reliable, and include a range of both self-reports and objective measures. Third, there has only been few studies evaluating the effect of psychological interventions on knee OA pain and no RCT’s evaluating the effect on patients with high levels of pain catastrophizing. Thus, good RCT’s are needed to determine the effectiveness.

There are some limitations as well. First, due to the different amount of attention paid to the patients in the two groups, a Hawthorne effect is possible [50, 51]. However, all patients will receive at least standard care which includes several contacts to both nurses, physiotherapists and doctors. Second, DXA scan, 30 s sit-to-stand and 6 MWT will be conducted after the first session in the intervention group. This procedure is chosen to be able to maintain the blinding of the physiotherapists by testing all the patients in the two groups the same day. However, the content of the first session is mostly introduction and since these outcome measures are not patient reported we do not think this will have an impact upon the results. Third, the patients will be randomized before baseline assessment. The reason for this is that the time between the patients are referred to a TKA and the operation is short and to be able to see the patients in the intervention group three times before the date for the operation this procedure is chosen. However, none of the patients are informed about the association between a high PCS score and long-term pain after TKA, so we don’t think this will affect the results.

We consider the external validity of the trial to be high while the treatment of TKA patients is almost similar all over the country. This makes it easier to implement at other Hospitals.

This project is expected to improve the overall treatment effect for a group of patients we today do not know how to treat the best way. We hope that this study can provide better functional outcome and less pain for the patients after the operation and that the study can produce new knowledge and inspire similar developments of interventions to other diseases.
